### Aims of This RCT

This study has three main aims: (1) to develop an ACT and compassion-based eHealth tool for CP management (iACTwithPain); (2) to analyze whether the iACTwithPain intervention will present superiority in improving CP’s impact and related health and quality-of-life markers over an ACT-only intervention and a wait-list condition; and (3) to examine whether the interventions’ efficacy will be explained by changes in therapeutic processes (e.g., self-compassion and psychological flexibility).

We hypothesize that the platform will present high acceptability and that both the ACT-only and iACTwithPain interventions will have efficacy in improving CP’s impact, mental health, and quality of life. Further, we also hypothesize that the intervention with explicit self-compassion components, the iACTwithPain, will present superiority in decreasing self-criticism and increasing self-compassion, quality of social relationships, and social safeness through the activation of the affiliative system and subsequent stimulation of oxytocin activity. The efficacy of the ACT-only intervention is expected to be explained by increases in psychological flexibility and mindfulness abilities, and decreases in cognitive fusion and rumination. The iACTwithPain intervention’s efficacy is expected to be explained by changes in the same processes and, in addition, by changes in self-compassion and self-criticism (Figure 1).

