### Sample Size

Results from G^∗^Power calculations for repeated measures analysis, assuming a *p*-value = 0.05, an effect size of *f* = 0.25 (Scott et al., 2018), with a statistical power of 0.95, three groups, and four measurements, recommend a sample size of 171. Giving the 30% drop-out rate in previous ACT-based intervention studies (Melville et al., 2010), the total sample size to be collected will be 246 (each group will be composed of 82 participants).

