### Randomization of Participants

Participants will be randomized (computer-generated random allocation) to one of three conditions: experimental condition 1 (ACT-only intervention); experimental condition 2 (iACTwithPain + self-compassion); and control condition (medical TAU). All participants will continue their treatment as usual for CP. Each participant will be randomly assigned with a number between 1 and 246; after number assignment, participants with numbers 1–82 will be allocated to experimental condition 1, 83–164 to experimental condition 2, and 84–246 to the control condition. Only participants from the experimental conditions will be blind to their allocation; we do not expect any need for unblinding participants in these conditions.

Participants in the two experimental conditions will then access to the respective version of the platform, where they will be asked to complete pre-intervention questionnaires (T0). The control group will only be provided access to the questionnaires.

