### The iACTwithPain Intervention

The iACTwithPain intervention (Table 1) will comprise core themes: (a) theme 1: pain acceptance (psychological flexibility in the presence of thoughts, feelings and behaviors associated with pain through mindfulness and acceptance practices); (b) theme 2: values-based action (promotion of behaviors consistent with personal goals, despite pain symptoms); and (c) theme 3: self-compassion (fostering a compassionate stance toward one’s struggles and suffering), which will only be incorporated in the intervention for experimental condition 2. These themes will be delivered through eight sessions that will be available to participants throughout an 8-week period. Each session will be composed of video-animations, real-image videos, complementary texts, and audio files with the experiential exercises/practices targeting the specific topic of the session. An introductory brief session (session 0) will welcome the participant to the intervention and guide him/her through the use of the platform. From session 1, all sessions will begin with a brief soft-landing exercise. Participants will be asked to complete between-session mindfulness and/or compassion-based meditative exercises as often as they can. These between-session assignments will aim to promote skills introduced in the previous session.

**TABLE 1 T1:** Overview of the iACTwithPain intervention.

**Session**	**Topics**	**In-session exercises/metaphors**	**Between-session assignments**
0	Introduction to the intervention and the platform	Contemplative exercise “Exploring my motivations to do this intervention”	–
1	Psycho-education about chronic pain; The problem with our problem-solving minds (controlling is the problem); Promotion of creative hopelessness; Introduction to mindfulness practice	Mindfulness of breathing practice	Mindfulness of breathing practice
2	Mindfulness as a key aspect to manage suffering; Therapists’ personal experience with mindfulness: Tips for maintaining regular practice; The body as an anchor to the present moment	Mindful movement exercise	Mindful movement exercise; Body scan practice
3	Exploration of the costs of trying to avoid/control pain; Promotion of willingness and acceptance	“What have I stopped doing because of pain?”; Passengers on a bus metaphor; Physicalizing exercise; Quicksand metaphor	Inviting a difficulty exercise

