### Implementation of the Interventions

Participants will follow the sessions in a given order (from session 1 to 8, one session per week). All data will be linked to a data hub tracking participants’ interaction with the platform (i.e., number of logins, duration of interaction with platform, number of visualization of videos/audios, and feedback on each session). Each week, participants will receive an email prompting them to login to the platform and complete the week’s session (that becomes available 1 week after the previous session was completed by the participant). Participants will also receive automatically generated reminders via email with supporting messages: (a) if they do not login for more than 3 days and (b) if they practice continuously (contingency management by reinforcing frequent engagement and practice). This will be particularly important to remind participants to practice the between-session assignments. Contact with the research team will be made available to participants during the intervention period through a one-to-one chat incorporated in the platform. As neither intervention will present risks to participants, a data monitoring committee is not expected to be involved. Adverse events are also not expected. Participants who skip more than two sessions will not be considered for the RCT (in the iACTwithPain group participants who do not complete both of the compassion sessions will be additionally excluded).

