### Statistical Analysis

The efficacy of the iACTwithPain will be assessed by comparing pre-intervention, post-intervention, and 3- and 6-month follow-up questionnaires’ scores through MANOVAs, repeated measures, within-between interaction (with Bonferroni correction). Changes in the primary outcome and in the secondary outcomes between pre-intervention, post-intervention, and follow-ups will be compared between the three conditions (iACT, iACTwithPain, and waiting-list). MANOVAs’ assumptions (multivariate normality, linearity, absence of multicollinearity, and equality of covariance matrices) will be analyzed prior to analysis.

Additionally, changes in painkillers dependence and hospital visits (self-disclosed) will also be compared between the three groups. Cohen’s *d* will be calculated to measure the between-group effect size on both primary and secondary outcomes. Changes in psychological processes (e.g., self-compassion, mindfulness, and psychological flexibility) will also be tested as potential mechanisms of change of the iACTwithPain intervention, using mediation modeling procedures. Missing data will be imputed with PASW Missing Value Analysis (SPSS Inc., United States) (Blankers et al., 2010).

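### Participants who skip more than two sessions are removed from the RCT after randomisation; only the active arms can lose people this way, so every active-control comparison can be biased

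*Protocol article*

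**What the plan says.** Under Implementation of the Interventions the article states: "Participants who skip more than two sessions will not be considered for the RCT". It adds that "in the iACTwithPain group participants who do not complete both of the compassion sessions will be additionally excluded". Under Randomization of Participants, allocation comes first and platform access follows; for the third arm, "The control group will only be provided access to the questionnaires".

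The second aim is to examine whether iACTwithPain is superior in improving pain impact and "related health and quality-of-life markers over an ACT-only intervention and a wait-list condition". The Statistical Analysis section compares change across the three conditions through the group-by-time interaction of a repeated-measures MANOVA, and says "Missing data will be imputed with PASW Missing Value Analysis". The Discussion adds that engagement data will be taken into account when efficacy is tested. No section limits the session rule to a per-protocol or sensitivity set, and none returns the excluded participants to the analysis.

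**The concern.** Session completion happens after randomisation and may be related to how a participant would fare in any arm. The rule removes poor attenders from two arms and cannot touch the third, which has nothing to attend. What is then compared is a selected part of each active arm against the whole control arm, and randomisation no longer protects that contrast. If poor attenders would have improved less regardless of treatment, dropping them makes both interventions look better than they are, even with no true effect. If people who feel better early stop attending, the interventions look worse.

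The rule also acts on sessions and not on missing outcomes. Someone who attends little but answers every questionnaire has nothing to impute and is still removed.

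**Working it through.** **1. The plan's own figure.** Inputs from Sample Size: f = 0.25, alpha 0.05, power 0.95, three groups, four measurements, 30% drop-out. For the interaction test with Pillai's trace, df1 = 2 × 3 = 6, df2 = 2 × (N − 3 − 3 + 2) and lambda = 0.0625 × N × 2. At N = 171, df2 = 334, lambda = 21.4 and power is 0.951. Then 171 / 0.70 = 244.3, rounded up to 245 and to 246 as a multiple of three, or 82 per arm. The sample size reproduces and is not in dispute.

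**2. Who can be removed.**

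- Control: no sessions, so 0 of 82.
- ACT-only: anyone completing fewer than six of the eight sessions.
- iACTwithPain: the same, plus the compassion-session condition.

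The asymmetry with control follows from the text and needs no assumption.

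**3. Bias formula.** Let p be the share of an active arm excluded and g the mean change among the retained minus the mean change among the excluded, with no treatment effect. The whole-arm mean is (1 − p) × retained + p × excluded = retained − p × g. The retained mean therefore exceeds the whole-arm mean by p × g. Control, kept whole, has the whole-arm mean in expectation, so bias = p × g.

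The gap has to be in change, because the planned test is on change. If the gap is g0 at T0 and g1 later, the retained means shift by p × g0 and p × g1, and the change shifts by p × (g1 − g0). A stable difference in level cancels.

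**4. Numbers.** Neither input is in the document. The only related figure comes from Sample Size ("Giving the 30% drop-out rate in previous ACT-based intervention studies"). It concerns drop-out, not skipped sessions, and is used here only as an upper value for p. It corresponds to 0.30 × 82 = 24.6, about 25 people per active arm. Bias in SD units:

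| Excluded | g = 0.2 | g = 0.3 | g = 0.5 |
|---|---|---|---|
| 10% | 0.02 | 0.03 | 0.05 |
| 20% | 0.04 | 0.06 | 0.10 |
| 30% | 0.06 | 0.09 | 0.15 |

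**5. Cross-check by a second model.** Let latent adherence correlate r with change, and let the least adherent share d be dropped. Bias is r × φ(z_d) / (1 − d), where z_d is the normal quantile at d and φ the normal density. With d = 0.10 and r = 0.1 it is 0.02 SD. With d = 0.30 it is 0.10 SD for r = 0.2 and 0.15 SD for r = 0.3. The range is about the same.

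**6. The compassion clause.** The compassion sessions are numbers 5 and 6. Sessions run in a fixed order, and each is one "that becomes available 1 week after the previous session was completed by the participant". If that is enforced, anyone who has completed six sessions has completed 1 to 6, so the clause removes nobody beyond the general rule.

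It matters only if sessions can be skipped singly. Assume each is skipped independently with probability 0.10:

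- ACT-only: P(Bin(8, 0.10) ≥ 3) = 3.8%, about 3 of 82.
- iACTwithPain, if missing either compassion session excludes: 1 − 0.90² × P(Bin(6, 0.10) ≤ 2) = 20.3%, about 17 of 82.
- iACTwithPain, if only missing both excludes: 3.8% + 0.10² × 0.90⁶ = 4.3%, about 4 of 82.

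So the difference between the active arms is nil under strict sequence, 0.5 percentage points under one reading of single skipping, and 16.5 points under the other.

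**The case against.** **An unseen analysis plan may analyse everyone.** It may, but that plan would then contradict the sentence in the article, which takes these people out of the RCT and not merely out of one analysis set. The wording needs correcting either way.

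**Imputation and the drop-out allowance already deal with this.** They do not. Imputation replaces missing outcomes and does not bring back someone with full questionnaires and few sessions. The 30% allowance protects power and does nothing about selection.

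**The false-positive rate.** A reader might infer that the rule raises the error rate to about 8% (30% excluded, gap 0.3 SD) or 14% (gap 0.5 SD). Those rates belong to a two-group comparison at one time point. The plan tests the interaction with time. If the same gaps are stable level differences already present at T0, a simulated test of change scores rejects in 4.8% and 5.0% of trials, so there is no inflation. This part of the objection stands, and no error rate is claimed here.

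**The test of what compassion adds.** A reader might infer from the compassion clause that iACTwithPain against ACT-only is tilted as well. The sequential release described in the article leaves that clause without effect, and its wording can also be read as applying only when both sessions are missed. The inequality is in the text; an effect on the result is not shown.

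**Slow participants and T1 timing.** The interventions are described as "eight sessions that will be available to participants throughout an 8-week period", while each release waits on the previous completion. A reader might infer that slow participants are excluded for pace, or that T1 moves later in the active arms. The article does not say whether access closes, whether sessions not reached count as skipped, or how T1 is anchored. These are details that an article may leave to the full protocol, so neither inference is supported.

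**Conclusion.** The concern holds for the active-control comparisons. The exclusion is stated without qualification, follows randomisation, depends on adherence, and cannot apply to control.

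Its size cannot be obtained from the document. The illustration is 0.09 SD, within 0.02 to 0.15 SD, and rests on an assumed excluded share and an assumed gap in change. The bias would favour the interventions if skippers would have improved less in any arm, and would go against them if early improvers skip more. It is zero if skippers and completers would have changed alike.

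The rule should be changed before analysis, because it touches every active-control comparison and the remedy is mostly wording.

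**What to change.** - Keep all 246 randomised participants in the primary comparison, in the arm to which they were allocated, whatever their session count. No new sample size is needed.
- Go on sending the T1 to T3 questionnaires to people who stop sessions, and impute only outcomes that are actually missing.
- Move session completion to a supplementary analysis, defined as at least six sessions and worded identically in both active arms. The separate compassion clause then goes.

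**Cost.** A revised paragraph and continued reminders to people who have stopped. The estimated effect may be smaller because low-exposure participants count, and more outcome data may need imputing. The gain depends on obtaining those questionnaires: where outcomes stay missing for reasons related to outcome, imputation does not guarantee an unbiased comparison.

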### Primary and Secondary Outcomes in the RCT

Before (T0) and after (T1) the interventions, and in the 3-month (T2) and 6-month (T3) follow-ups, participants in the experimental conditions and in the waiting-list control condition will be assessed through several self-report questionnaires. Participants will receive notifications via email to complete the self-report measures. These data will be collected in the iACTwithPain platform using high standard security mechanisms which will ensure confidentiality. Only the research team will have access to the collected data, including the final dataset, which will be managed by the study’s PI (PC) and kept for 5 years after the study ends. Participants will only be identified by a generated code.

Participants will provide sociodemographic and clinical information and complete self-report measures (in their validated Portuguese versions) to assess primary and secondary outcomes see Table 2.

**TABLE 2 T2:** Schedule of enrollment, interventions, and assessments.

	**Study period**					
	**Enrollment**	**Allocation**	**Post-allocation**			
**Timepoint**	** *-t_2_* **	** *-t_1_* **	** *t* _0_ **	** *t* _1_ **	** *t* _2_ **	** *t* _3_ **
**Enrollment**						
*Informed consent*	X					
*Eligibility screen*	X					
*Blinded randomization*	X					
*Allocation*		X				
**Interventions**						
*iACTwithPain*						
*ACT-only intervention*						
*Waiting list*						
**Assessments**						
*Primary outcome*						
*PIQ*			X	X	X	X
*Secondary outcomes*						
*MPQ*			X	X	X	X
*HADS*			X	X	X	X
*WHOQOL-bref*			X	X	X	X
*RRQ*			X	X	X	X
*FSCRS*			X	X	X	X
*SCS*			X	X	X	X
*SSPS*			X	X	X	X
*CAMS-R*			X	X	X	X
*CFQ-7*			X	X	X	X
*CompACT*			X	X	X	X
*Intervention’s acceptability questions**				X		

**only for the active conditions.*

#### Primary Outcome

##### Pain impact

The six-item Pain Impact Questionnaire (PIQ-6; Becker et al., 2007; Cavalheiro et al., 2011) will be used to assess participants’ perceived pain severity (1 item rated on a 6-point scale) and impact on emotional well-being, leisure activities, and work functioning (five items rated on a 5-point scale).

#### Key Mediators

##### ACT-Related Variables

Psychological flexibility, as conceptualized by ACT, will be measured by the comprehensive assessment of ACT processes (CompACT; Francis et al., 2016; Trindade et al., under review), an 18-item measure with three subscales: openness to experience, behavior awareness, and valued action, in which items are rated on a 7-point response scale (0—“Strongly disagree” to 6—“Strongly agree”). Mindfulness abilities will be measured using the Cognitive and Affective Mindfulness Scale-Revised (CAMS-R; Feldman et al., 2007; Teixeira et al., 2017) which presents 12 items answered on a 4-point Likert scale from 1 (Not at all) to 4 (Almost always). Cognitive fusion will be assessed by the seven-item Cognitive Fusion Questionnaire (CFQ-7; Gillanders et al., 2014; Pinto-Gouveia et al., 2020), in which the response scale ranges from 1 (“Never true”) to 7 (“Always true”).

##### Rumination

This outcome will be assessed by the Ruminative Responses Questionnaire (RRQ; Treynor et al., 2003; Dinis et al., 2011), a 10-item measure with two subscales, reflective rumination and brooding, which are rated on a 4-point Likert scale (0—Almost Never; 3—Almost Always).

##### Self-criticism, self-reassurance, self-compassion, and social safeness

Self-criticism will be measured by the Forms of Self-Criticizing/Attacking and Self-Reassuring Scale (FSCSR; Gilbert et al., 2004; Castilho et al., 2015b), a scale with 22 items measuring self-criticism (inadequate self and hated self) and the ability to self-reassure. Respondents rate items on a 5-point Likert scale (0 = not at all like me; 4 = extremely like me). Further, the Self-Compassion Scale (SCS; Neff, 2003; Castilho et al., 2015a) will provide the measurement of self-compassion. The SCS is composed of 26 items that assess six components: Self-Kindness, Self-Judgment, Common Humanity, Isolation, Mindfulness, and Over-Identification. Each item is rated on a 5-point Likert scale accordingly to how frequently participants act that way toward themselves in difficult times (1—“Almost never” to 5—“Almost always”). To assess social safeness, the Social Safeness and Pleasure Scale (SSPS; Gilbert et al., 2009) will be used. This is a 11-item instrument that measures, on a 5-point Likert scale, current feelings of safeness, belonging, acceptance, and a sense of connectedness.

#### Secondary Outcomes

##### Quality and Intensity of Subjective Pain

The McGill Pain Questionnaire (MPQ; Melzack, 1975; Figueiral, 2002), a three-part pain assessment tool, will be used to evaluate several dimensions of the participants’ pain experience—location, intensity, and verbal description.

##### Psychological Functioning

Anxiety and depression symptoms will be assessed by the Hospital Anxiety and Depression Scales (HADS; Zigmond and Snaith, 1983; Pais-Ribeiro et al., 2007), in which participants rate the 14 items (7 items for each subscale) on a 4-point scale between 0 and 3 (the scale varies). For each subscale, scores between 0 and 7 are considered normal, 8–10 mild, 11–14 moderate, and 15–21 severe.

##### Quality of life

To assess this outcome, the World Health Organization Quality of Life—Bref (The WHOQOL Group, 1998; Vaz Serra et al., 2006), a 26-item multidimensional measure of subjective quality of life, will be used. This instrument measures four dimensions of quality of life (physical, psychological, social relations, and environment) on a 5-point Likert scale.

### Acceptability Assessment

The intervention’s acceptability will be assessed in the experimental conditions by analyzing (a) participants’ adherence (attrition rate) and (b) results from the Client Satisfaction Questionnaire (Attkisson and Zwick, 1982) adapted to the eHealth intervention context.

### Statistical Analysis

The efficacy of the iACTwithPain will be assessed by comparing pre-intervention, post-intervention, and 3- and 6-month follow-up questionnaires’ scores through MANOVAs, repeated measures, within-between interaction (with Bonferroni correction). Changes in the primary outcome and in the secondary outcomes between pre-intervention, post-intervention, and follow-ups will be compared between the three conditions (iACT, iACTwithPain, and waiting-list). MANOVAs’ assumptions (multivariate normality, linearity, absence of multicollinearity, and equality of covariance matrices) will be analyzed prior to analysis.

Additionally, changes in painkillers dependence and hospital visits (self-disclosed) will also be compared between the three groups. Cohen’s *d* will be calculated to measure the between-group effect size on both primary and secondary outcomes. Changes in psychological processes (e.g., self-compassion, mindfulness, and psychological flexibility) will also be tested as potential mechanisms of change of the iACTwithPain intervention, using mediation modeling procedures. Missing data will be imputed with PASW Missing Value Analysis (SPSS Inc., United States) (Blankers et al., 2010).

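### The efficacy test uses T0 as one of four repeated outcomes rather than as a baseline covariate; this is valid but gives up precision on the pairwise comparisons the trial is about

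*Protocol article*

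**What the plan says.** The Statistical Analysis section of the protocol article assesses efficacy by "comparing pre-intervention, post-intervention, and 3- and 6-month follow-up questionnaires’ scores". The method is given as a comparison of "scores through MANOVAs, repeated measures, within-between interaction (with Bonferroni correction"). It adds: "Changes in the primary outcome and in the secondary outcomes between pre-intervention, post-intervention, and follow-ups will be compared between the three conditions". The pre-intervention score (T0) is therefore one of four levels of the time factor, and no baseline covariate is mentioned. The same section plans a between-group Cohen's d for primary and secondary outcomes, and states: "Missing data will be imputed with PASW Missing Value Analysis".

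The Sample Size section gives the inputs "assuming a *p*-value = 0.05, an effect size of *f* = 0.25" and continues "with a statistical power of 0.95, three groups, and four measurements, recommend a sample size of 171". The total is then raised to 246 (82 per arm) for 30% drop-out. Aim 2 in Aims of This RCT is superiority of iACTwithPain over ACT-only and over the control condition.

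**The concern.** When T0 is an outcome level, the arm-by-time interaction compares changes from T0. In a randomised trial, putting T0 in the model as a covariate targets the same arm difference with smaller variance. The plan already collects T0, so the lost precision buys nothing.

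Precision matters most for iACTwithPain against ACT-only. The two programmes differ only in sessions 5 and 6, so the difference may well be small. The planned interaction pools three arms and four times in one test, and a significant result does not say which arms differ or when. The MANOVA also needs a full row of four scores per participant, which makes the result lean on imputation if 30% drop out.

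**Working it through.** **1. Which test was planned.** Inputs from Sample Size: alpha 0.05, f = 0.25, power 0.95, 3 groups, 4 measurements. For the Pillai test of a within-between interaction there are 3 time contrasts and 2 group contrasts, so s = 2 and df1 = 3 × 2 = 6. The other terms are df2 = s(N − 3 − 3 + s) and noncentrality = N·s·f².

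- N = 171: df2 = 2 × 167 = 334; noncentrality = 171 × 2 × 0.0625 = 21.375; power 0.951.
- N = 170: power 0.9499, just below target.

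So 171 is exactly the repeated-measures MANOVA figure. The alternatives tried do not give it: a repeated-measures ANOVA interaction gives 45 at correlation 0.5, or 117 with the other effect-size convention; the between-groups test gives 159 at correlation 0.5; a one-way ANOVA gives 252. Sample size and analysis agree with each other.

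**2. Drop-out.** 171/0.7 = 244.3, so 245, or 246 for three equal arms. Conversely 246 × 0.7 = 172.2, and 172 complete rows give power 0.953 at f = 0.25.

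**3. Precision at one follow-up visit.** The correlation rho between T0 and follow-up is not in the protocol. I assume equal variances (set to 1) and show a range.

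- Change from T0: variance 2(1 − rho).
- T0 as covariate: variance 1 − rho².
- Ratio: (1 − rho²)/[2(1 − rho)] = (1 + rho)/2, which is below 1 for every rho below 1.

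| rho | change | adjusted | reduction |
|---|---|---|---|
| 0.3 | 1.40 | 0.91 | 35% |
| 0.5 | 1.00 | 0.75 | 25% |
| 0.6 | 0.80 | 0.64 | 20% |
| 0.7 | 0.60 | 0.51 | 15% |
| 0.8 | 0.40 | 0.36 | 10% |

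**4. Illustrative pairwise power.** 57 per arm (171/3), an assumed difference of 0.5 SD, two-sided noncentral t with 112 df. At rho = 0.5 the noncentrality is 0.5/√(1.00 × 2/57) = 2.67 for change and 0.5/√(0.75 × 2/57) = 3.08 with adjustment. The protocol does not say how many tests the Bonferroni correction covers, so 0.05/3 is a further assumption.

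| rho | alpha 0.05: change → adjusted | alpha 0.05/3: change → adjusted |
|---|---|---|
| 0.3 | 0.61 → 0.79 | 0.43 → 0.64 |
| 0.5 | 0.75 → 0.86 | 0.60 → 0.74 |
| 0.7 | 0.93 → 0.96 | 0.84 → 0.90 |
| 0.8 | 0.99 → 0.99 | 0.96 → 0.98 |

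**5. Match to the aim.** Aim 2 names two pairwise contrasts. The planned interaction test has 6 df, and the 0.95 power in Sample Size belongs to that omnibus test, not to either contrast.

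**The case against.** The strongest defence is that nothing here is an error. The arm-by-time test is valid under randomisation, the choice does not by itself bias the comparison, and the sample size was computed for this very test. All of that stands.

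Three stronger readings are tempting, and the protocol does not support them.

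- *The analysis will throw away incomplete participants.* The Statistical Analysis section plans imputation, and 246 already allows for 30% drop-out. Even an analysis of complete rows only would keep the planned power for the omnibus test (step 2). What remains is that the result depends on imputed values, where a mixed model would use the observed visits directly.
- *The trial will report a p-value and no treatment effect.* A between-group Cohen's d is planned. What remains is that it is not stated to be baseline-adjusted, and that the omnibus test alone does not settle the pairwise question.
- *The trial is underpowered, or loses a known amount of power.* The direction of the loss is certain for any correlation below 1, but its size is not. The correlation, the 0.5 SD pairwise difference and alpha 0.05/3 are all assumptions. At correlation 0.8 the gain in power is very small. Larger savings can be computed for the mean of T1 to T3, but the protocol specifies no such contrast.

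The benefit of adjustment also presupposes a clean T0. In Randomization of Participants and in Table 2, T0 comes after allocation, and controls know their arm. That weakness affects change scores as well, so it does not favour the planned analysis.

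**Conclusion.** The point holds as an efficiency improvement that should be made; it does not show an invalid analysis. Treating T0 as an outcome level costs precision that a covariate would recover: 35% to 10% of the variance at one visit for an assumed correlation of 0.3 to 0.8, and 25% at 0.5, given equal variances at T0 and follow-up. The pairwise power figures are illustrations under the assumptions stated with them. Two further weaknesses come with the choice: the 6-df test does not by itself answer the superiority aim, and the need for complete rows makes the result depend on the planned imputation.

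**What to change.** For PIQ-6, and likewise for each secondary scale, fit a linear mixed model to the T1 to T3 scores with arm, visit, arm-by-visit, T0 score and T0-by-visit, and an unstructured covariance. Include all randomised participants with any follow-up value. Report adjusted pairwise arm differences with 95% confidence intervals, with one visit named as primary (the article names none). Keep the MANOVA as a supportive analysis if wanted. Collect T0 before allocation is disclosed.

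Inclusion of all randomised participants must be squared with the rule in Implementation of the Interventions that leaves out those who skip more than two sessions.

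Cost: analysis wording, different code, a change in when T0 is completed, and reliance on a missing-at-random assumption. No added participants or measurements.
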